#### **7.1.7.1.2 Device defects.**

#### **7.1.7.1.3 Other adverse events.**

### **7.1.7.2 Methods and Timing for Evaluating, Recording, and Analyzing Safety Parameters**

**7.1.7.2.1** Serious adverse events related to the trial device are defined as events determined by the independent clinical event committee to be related, definitely related, or possibly related to the trial device, including:

- All-cause mortality: Cardiovascular and non-cardiovascular deaths from any cause.
- Cardiovascular death related to the trial device: Defined according to the Valve Academic Research Consortium (VARC) as death due to cardiac causes (e.g., myocardial infarction, cardiac tamponade, worsening heart failure), non-coronary vascular disease, surgery-related deaths (including deaths related to surgical complications or their treatment), sudden or unexplained deaths.
- Major bleeding related to the trial device: Defined according to the Bleeding Academic Research Consortium (BARC) as type 3b or higher bleeding (excluding type 4).

| Type | Explain |
|------|---------|
| 0    | NH      |

|                         |    |                                                                                                                                                                                                                                                                                                                                                                                                                          |
|-------------------------|----|--------------------------------------------------------------------------------------------------------------------------------------------------------------------------------------------------------------------------------------------------------------------------------------------------------------------------------------------------------------------------------------------------------------------------|
| 1                       |    | Non-active bleeding that does not result in a visit to a physician; may include bleeding that results in a patient discontinuing a medication without medical advice                                                                                                                                                                                                                                                     |
| 2                       |    | Any significant active bleeding symptoms (e.g., bleeding greater than the expected amount, including bleeding found only on imaging), excluding bleeding that fits type 3, 4, or 5, and meeting one of the following criteria: 1) bleeding requiring non-surgical medical intervention by a healthcare provider, 2) bleeding resulting in hospitalization or high-level care, or 3) bleeding requiring urgent evaluation |
| 3                       | 3a | There are obvious bleeding symptoms and HGB decreased by 3- 5g/dL (the correlation between HGB decrease and bleeding needs to be determined). There is obvious bleeding that requires blood transfusion                                                                                                                                                                                                                  |
|                         | 3b | Significant bleeding symptoms and a decrease in HGB of at least 5g/dL (the correlation between the decrease in HGB and bleeding needs to be determined); cardiac tamponade; bleeding requiring surgical hemostasis (excluding bleeding from gums/nasal cavity/skin/hemorrhoids); bleeding requiring the use of vasoactive drugs                                                                                          |
|                         | 3c | Intracranial hemorrhage (excluding microbleeds or hemorrhagic transformation; but including intradural hemorrhage); subtypes of bleeding determined by autopsy or imaging or lumbar puncture; blindness caused by intraocular hemorrhage                                                                                                                                                                                 |
| 4 CABG-related bleeding |    | Intraoperative intracranial hemorrhage occurring within 48 hours; bleeding requiring re-thoracotomy for hemostasis, transfusion of $\geq 5U$ of packed red blood cells or whole blood within 48 hours; thoracic drainage $> 2L$ within 24 hours                                                                                                                                                                          |
| 5 Fatal bleeding        | 5a | Possible fatal bleeding; non-pathological or imaging basis but clinically suspicious                                                                                                                                                                                                                                                                                                                                     |
|                         | 5b | Determine the presence of fatal bleeding with obvious signs of bleeding or with pathological or imaging evidence                                                                                                                                                                                                                                                                                                         |

- Severe damage to cardiac or other body structures related to the trial device.
- Infective endocarditis related to the trial device.
- Thromboembolic events related to the trial device: Defined as myocardial

infarction, cerebral infarction, or organ embolism caused by thrombosis, with clinical or imaging evidence of arterial occlusion.

**7.1.7.2.2** Surgical details and intraoperative complications will be recorded in the electronic case report form (eCRF). Safety evaluations will be conducted at discharge/30 days, 3 months, 6 months, 12 months, and annually from 2 to 5 years postoperatively, recording all adverse events. All eCRF data will be submitted to the statistical center for clinical data analysis and evaluation.

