| Secondary endpoint | 
1 At discharge or 30 days postoperatively (whichever comes first), 3 months, 6 months, and 12 months:
 
1.1 Degree of valve regurgitation assessed by echocardiography (evaluated according to the tricuspid regurgitation assessment index table).
 
1.2 Changes in echocardiographic parameters (right atrial and ventricular size, diameter, width of the narrowest regurgitation jet, and revers.
 
1.3 NYHA functional class.
 
1.4 Freedom from reoperation due to tricuspid valve insufficiency.
 
2 Evaluation of the trial device's performance, including needle insertion smoothness and user-friendliness of the ring holder.
 
3 Technical success rate of the surgery (before leaving the operating room), defined as no intraoperative death, successful implantation of the annuloplasty ring, successful removal of the ring holder, and no emergency surgery or secondary intervention related to the trial device.
 
4 At discharge or 30 days postoperatively (whichever comes first), 3 months, 6 months, and 12 months:
 
4.1 Incidence of serious adverse events, including cardiovascular death, major bleeding, severe damage to cardiac or other body structures, infective endocarditis, and thromboembolic events related to the trial device.
 
4.2 All-cause mortality.
 
4.3 Cardiovascular death related to the trial device.
 
4.4 Major bleeding related to the trial device.
 
4.5 Severe damage to cardiac or other body structures related to the trial device.
 
4.6 Infective endocarditis related to the trial device.
 
4.7 Thromboembolic events related to the trial device.
 
5 Device defects.
 
6 Other adverse events.
 |

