Biomedical Engineering Co., Ltd., while the control group will use the cardiac annuloplasty ring manufactured by Edwards Lifesciences (Shanghai) Medical Products Co., Ltd., for tricuspid valve annuloplasty. Imaging and/or clinical follow-up will be performed intraoperatively, before discharge or 30 days  $\pm$  7 days postoperatively, 3 months  $\pm$  15 days postoperatively, 6 months  $\pm$  30 days postoperatively, and 12 months  $\pm$  30 days postoperatively. The primary study endpoint is the success rate of annuloplasty ring repair at 6 months after surgery, defined as the absence of severe regurgitation and  $\leq$  15% increase in radial line value (based on a comprehensive determination of the degree of regurgitation and increase in radial line value) as evaluated by echocardiography. Secondary effectiveness evaluation endpoints include the degree of regurgitation indicated by cardiac ultrasound before discharge or at 30 days after operation (whichever comes first), and at 3, 6, and 12 months after operation, changes in echocardiographic parameters (right atrium size, right ventricular size, diameter value, width of the narrowest part of the regurgitant bundle, and reverse flow area), NYHA functional classification, and freedom from reoperation of the tricuspid valve due to tricuspid insufficiency. Performance evaluation of the test device includes smooth needle insertion and ease of use of the ring holding device and technical success rate of the operation (before leaving the operating room), defined as no intraoperative death, successful ring implantation, and holding Successful removal of the device without emergent procedure or secondary intervention related to the investigational device; Safety endpoints included the incidence of serious adverse events (such as cardiovascular death related to the investigational device, major bleeding, major damage to cardiac or other body structures, infective endocarditis, thromboembolic events), all-cause death, cardiovascular death related to the investigational device, major bleeding related to the investigational device, major damage to cardiac or other body structures related to the investigational device, infective endocarditis related to the investigational device, thromboembolic events related to the investigational device, device defects, and other adverse events occurring before discharge or within 30 days after the procedure, whichever came first. Follow-up assessments included clinical symptoms and signs, laboratory examinations, ECG, color Doppler ultrasound, and recording of adverse events, all aimed at verifying the safety and effectiveness of the investigational annuloplasty ring.

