### **7.1.7 Safety Evaluation Methods**

#### **7.1.7.1 Description of Safety Parameters**

Safety endpoints:

**7.1.7.1.1** At discharge or 30 days postoperatively (whichever comes first), 3 months, 6 months, and 12 months:

- Incidence of serious adverse events, including cardiovascular death, major

bleeding, severe damage to cardiac or other body structures, infective endocarditis, and thromboembolic events related to the trial device.

- All-cause mortality.
- Cardiovascular death related to the trial device.
- Major bleeding related to the trial device.
- Severe damage to cardiac or other body structures related to the trial device.
- Infective endocarditis related to the trial device.
- Thromboembolic events related to the trial device.

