##### **8.1.6.2 Secondary Safety Endpoint Analysis**

**8.1.6.2.1** The incidence of device-related serious adverse events (SAEs) at discharge or 30 days, 3 months, 6 months, and 12 months post-surgery will be compared between groups using the chi-square test or Fisher's exact test.

**8.1.6.2.2** The incidence of all-cause mortality at discharge or 30 days, 3 months, 6 months, and 12 months post-surgery will be compared using the chi-square test or Fisher's exact test.

**8.1.6.2.3** The incidence of cardiovascular death related to the test device at discharge or 30 days, 3 months, 6 months, and 12 months post-surgery will be compared using the chi-square test or Fisher's exact test.

**8.1.6.2.4** The incidence of major bleeding related to the test device at discharge or 30 days, 3 months, 6 months, and 12 months post-surgery will be compared using the chi-square test or Fisher's exact test.

**8.1.6.2.5** The incidence of severe damage to cardiac or other body structures related to the test device at discharge or 30 days, 3 months, 6 months, and 12 months post-surgery will be compared using the chi-square test or Fisher's exact test.

**8.1.6.2.6** The incidence of device-related infective endocarditis at discharge or 30 days, 3 months, 6 months, and 12 months post-surgery will be compared using the chi-square test or Fisher's exact test.

**8.1.6.2.7** The incidence of thromboembolic events related to the test device at discharge or 30 days, 3 months, 6 months, and 12 months post-surgery will be compared using the chi-square test or Fisher's exact test.

**8.1.6.2.8** The incidence of adverse events from postoperative to 5-year follow-up will be compared using the chi-square test or Fisher's exact test.

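### The secondary device-related SAE composite is defined inconsistently across sections: whether all-cause death belongs to it, how long its window runs, and which ring the events must relate to

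*Protocol*

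**What the plan says.** **Composite as an endpoint.** The Synopsis (secondary endpoint 4.1) gives the composite as "Incidence of serious adverse events, including cardiovascular death, major bleeding, severe damage to cardiac or other body structures", followed by infective endocarditis and thromboembolic events, related to the trial device. All-cause mortality is its own item, 4.2. Section 7.1.7.1.1 has the same structure.

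**Composite as an operational rule.** Section 7.1.7.2.1 is the only place that says how an event qualifies: "Serious adverse events related to the trial device are defined as events determined by the independent clinical event committee to be related, definitely related". A merely possible link to the ring is enough as well. The list under that stem opens with "All-cause mortality: Cardiovascular and non-cardiovascular deaths from any cause".

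**Window.** Section 7.1.7.1.1 sets it as "At discharge or 30 days postoperatively (whichever comes first), 3 months, 6 months, and 12 months". Section 3.2 recites the same safety endpoints and ends them with "occurring before discharge or within 30 days after the procedure, whichever came first", with no later time point.

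**Which ring.** The Synopsis and Section 7.1.4 call only the sponsor's ring the investigational device; the MC3 ring is the control device. Section 8.1.6.2 nevertheless plans between-arm tests on items such as "The incidence of major bleeding related to the test device at discharge or 30 days" and the later visits.

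**The concern.** An event committee needs one rule, because it classifies events while the trial runs. Section 7.1.7.2.1 gives it two that conflict: the stem requires a link to the device, and the first item takes in death from any cause. A statistical analysis plan written later can choose which events to tabulate, but it does not by itself undo classifications already made under an unclear definition.

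The window and the device wording add to this. A reader of Section 3.2 would stop counting at discharge or 30 days; a reader of Section 8.1.6.2 would go on to 12 months. A reader who takes the test or investigational device literally would ask about relatedness in one arm only. Safety is half of the stated objective, and the 6-month summary report goes to the regulator for registration, so the rate per arm should not depend on which section was followed.

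**Working it through.** The protocol states no expected rate, power or sample size for any safety endpoint, so there is no planned figure to reproduce. The sample size in Section 8.2 rests on efficacy alone. The check is therefore a comparison of texts.

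**Step 1: the sections side by side.** Early means discharge or 30 days, whichever is first.

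| Place | All-cause death | Window | Ring named |
|---|---|---|---|
| Synopsis, secondary endpoints 4.1 to 4.7 | separate | early, 3, 6, 12 months | trial device |
| Synopsis, Trial Design | separate | early, 3, 6, 12 months | investigational device |
| 3.2 | separate | early only | investigational device |
| 7.1.2.3 | separate | early, 3, 6, 12 months | the device |
| 7.1.7.1.1 | separate | early, 3, 6, 12 months | trial device |
| 7.1.7.2.1 | **inside the list** | none in the definition | trial device |
| 7.1.8.4 | separate | early, 3, 6, 12 months | trial device |
| 8.1.6.2 | separate (8.1.6.2.2) | early, 3, 6, 12 months | device-related in two items, test device in four |

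One place in eight puts all-cause death inside. One place ends the window early.

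**Step 2: what the 7.1.7.2.1 list can mean.**

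- *The stem governs.* Only deaths judged related count. This still differs from the five-component endpoint, because a related non-cardiovascular death that fits no other component would count here and not there.
- *The item governs.* Every death counts, whatever the committee decides.
- *The list is a glossary.* All-cause mortality is defined there but is not a component.

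The text does not say which is meant.

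**Step 3: direction.** Let c be the rate of the five device-related components and d the rate of other deaths, treated as independent. With deaths out the composite is c. With all deaths in it is 1 − (1 − c)(1 − d) = c + d(1 − c), which exceeds c whenever d > 0 and c < 1.

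**Step 4: why no size follows.** Neither c nor d is in the protocol. Assume c from 1% to 5% and d from 2% to 10%, with 82 patients per arm:

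- c = 5%, d = 2%: 1 − 0.95 × 0.98 = 6.9%, or 1.4 times c (82 × 0.05 = 4.1 against 82 × 0.069 = 5.7 patients).
- c = 1%, d = 10%: 1 − 0.99 × 0.90 = 10.9%, or 10.9 times c (82 × 0.01 = 0.8 against 82 × 0.109 = 8.9 patients).

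A factor between 1.4 and 10.9, all of it assumed, establishes the direction and nothing more. It also applies only if the item overrides the stem.

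**Step 5: relatedness levels.** Section 13.1 has five levels: certain, likely, possible, may not be relevant, irrelevant. The 7.1.7.2.1 stem has three qualifying labels: related, definitely related, possibly related. Plain related has no counterpart on the scale and likely is not named, so the mapping has to be inferred.

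**The case against.** The strongest reply is that the intended endpoint is recoverable. The six items in 7.1.7.2.1 follow the order of the last six bullets in 7.1.7.1.1, which suggests a glossary that was wrongly nested. Section 8.1.6.2 analyses device-related SAEs and all-cause mortality separately. Section 3.2 itself schedules follow-up with adverse-event recording to 12 months, and long-term safety follow-up to 5 years, so its short window looks like a dropped phrase. All of this stands, and it limits the point to an inconsistency of definition. It does not make the contradictory text correct.

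Several stronger readings are tempting, and the documents do not support them:

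- *The composite would be dominated by deaths unrelated to either ring.* The stem, if applied, keeps such deaths out. The only mortality figure for the control ring is a cited series with 4 deaths in 75 patients (4/75 = 5.3%; Section 4.2 prints 53%) and follow-up averaging 16 months. It is not a planning assumption for this trial.
- *This is the trial's main safety rate.* Section 8.9 mentions primary safety metrics but names none, and the composite is listed among the secondary endpoints.
- *Later safety data would be lost.* Adverse events are recorded through 5 years under 7.1.7.2.2, and the analysis section runs to 12 months.
- *Controls would be fixed at zero events.* Section 8.1.6.2 compares groups throughout and uses the neutral term device-related in two items. The literal reading is almost certainly not meant.
- *Likely-related events are excluded.* Plain related can reasonably cover them. This is loose wording that needs a mapping.

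**Conclusion.** The point holds as an inconsistency in a secondary safety endpoint. Section 7.1.7.2.1 contradicts the rest of the protocol on all-cause death, and its own stem as well. Section 3.2 contradicts the other sections on the window. The investigational or test device wording does not fit a comparison in which controls carry a different ring. The all-cause-death conflict is the strongest of the three, because it sits in the definition the event committee would apply; the window conflict rests on Section 3.2 alone.

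The primary decision does not move: Section 8.5 makes trial success depend only on the 6-month repair success rate. No size can be attached to the effect on the safety composite, because the protocol gives no safety rates. Counting unrelated deaths would raise it under any positive rate of such deaths. The correction is worth making, since it is cheap and is best settled before events are adjudicated.

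**What to change.** - Take all-cause mortality out of the 7.1.7.2.1 list and keep it as its own endpoint, as 7.1.7.1.1 and 8.1.6.2.2 already do.
- Add the 3-, 6- and 12-month time points to the safety sentence in Section 3.2.
- Define relatedness as relation to the implanted study ring, test or control, and use that term in the Synopsis and in Sections 3.2, 7.1.7 and 8.1.6.2.
- State which Section 13.1 levels qualify, so that the committee's categories map one to one onto that scale.
- Count events cumulatively by event date, so that the early window does not close at a different discharge date for each patient. The visit schedule need not change.

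The cost is a minor protocol edit and a re-mapping of the adjudication categories. No new data are needed, because all adverse events are already recorded.

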### **7.1.8 Trial Endpoints**

Primary endpoint: The success rate of valve annuloplasty repair at 6 months postoperatively, defined as no severe regurgitation and an increase in diameter  $\leq 15\%$  (based on a comprehensive assessment of regurgitation severity and diameter increase).

Secondary endpoints:

**7.1.8.1** At discharge or 30 days postoperatively (whichever comes first), 3 months, 6 months, and 12 months:

**7.1.8.1.1** Degree of valve regurgitation assessed by echocardiography (evaluated according to the tricuspid regurgitation assessment index table).

**7.1.8.1.2** Changes in echocardiographic parameters (right atrial and ventricular size, diameter, width of the narrowest regurgitation jet, and reverse flow area).

**7.1.8.1.3** NYHA functional class.

**7.1.8.1.4** Freedom from reoperation due to tricuspid valve insufficiency.

**7.1.8.2** Evaluation of the trial device's performance, including needle insertion smoothness and user-friendliness of the ring holder.

**7.1.8.3** Technical success rate of the surgery (before leaving the operating room), defined as no intraoperative death, successful implantation of the annuloplasty ring, successful removal of the ring holder, and no emergency surgery or secondary intervention related to the trial device.

**7.1.8.4** At discharge or 30 days postoperatively (whichever comes first), 3 months, 6 months, and 12 months:

**7.1.8.4.1** Incidence of serious adverse events, including cardiovascular death, major bleeding, severe damage to cardiac or other body structures, infective endocarditis, and thromboembolic events related to the trial device.

**7.1.8.4.2 All-cause mortality.**

**7.1.8.4.3 Cardiovascular death related to the trial device.**

**7.1.8.4.4 Major bleeding related to the trial device.**

**7.1.8.4.5 Severe damage to cardiac or other body structures related to the trial device.**

**7.1.8.4.6 Infective endocarditis related to the trial device.**

